# Rationale for the study

Cardiac rehabilitation after myocardial infarction or coronary syndrome, whether or not followed by percutaneous or surgical revascularisation, continues to be recognised in the latest guidelines and recommendations published by the major scientific societies as a class I^1,2^. These programs were proposed by the World Health Organisation in the 1960s to improve the quality of life and prognosis of patients with heart disease. The cardiac rehabilitation includes, in addition to a physical training program, guidelines for healthy nutrition, psychological counselling and stress management. This, together with pharmacological treatment, constitutes the best clinical practice in cardiovascular prevention for our patients. Despite this evidence, the number of patients joining these programs in Europe is still less than 30%, a figure that is reduced in Spain to a symbolic 3%, according to data from the EUROASPIRE III study^3^. According to this study, 17% of those surveyed after a coronary event still smoked; 35% were obese; 56% had hypertension and 51% had dyslipidaemia. Considering that the measures carried out in these rehabilitation programs are very cost-effective in reducing cardiovascular risk, it is difficult to understand why they have not received greater impetus from health authorities and professionals involved so far. Instead, the impact of pharmacological prevention measures, enhanced in recent years, has contributed to drastically improve the prognosis of patients after acute coronary syndrome, partly diminishing the weight of evidence for the benefit of cardiac RHB programs^4,5^. In two of the latest prospective trials, cardiac BHR programs failed to demonstrate positive results on the primary endpoint (total mortality, myocardial infarction and hospital readmission), although they were superior on some secondary endpoints such as non-fatal infarction or length of hospital stay^6,7^. Taylor et al, in 2004 noted that the benefit of cardiac RHB with exercise alone was 16% in terms of cardiovascular mortality. If it was also incorporated into a comprehensive program, including risk factor control and educational measures, the benefit amounted to 24% ^8^. In a later published meta-analysis, the authors estimated that half of the 28% reduction in cardiac mortality achieved was attributable to the reduction in major risk factors and, therefore, there was no independent risk reduction due to physical exercise alone ^9^. Martin et al, in a prospective cohort study, showed that subjects (n=2900) who completed a full rehabilitation program had a lower risk of death, cardiac and overall hospitalisation compared to those subjects (n=554) who did not^10^. Suaya et al, in an analysis to control for a number of variables in participants and non-participants in BHR programs, among 60,000 coronary subjects over 65 years of age included in MEDICARE, observed a 21-34% reduction in 5-year mortality in BHR program users compared to non-users^11^. Unfortunately, in this multidisciplinary program the impact of physical exercise on mortality reduction was not specifically analysed. In any case, it seems that the benefit of physical exercise is inseparable from the other measures. Therefore, the European and American guidelines on cardiovascular prevention describe the recommendations for physical activity and participation in rehabilitation programs in separate sections. Moreover, the benefit of cardiac rehabilitation programs is directly related to the length of time the patient remains in the program. This relationship has been analysed in 3,161 patients with a recent coronary event included in the Medicare database, who attended at least one rehabilitation session. After 4 years of follow-up, patients who attended 36 sessions had a 14% lower risk of death and a 12% lower risk of myocardial infarction than those who attended 24 sessions; a 22% lower risk of death and a 23% lower risk of myocardial infarction than those who attended 12 sessions; and 47% lower risk of death and 31% lower risk of myocardial infarction than those who attended only one session. However, only 18% of patients completed the maximum of 36 sessions^12^. On the other hand, it appears that health-related quality of life does not differ in relation to the duration of the 6-month rehabilitation program compared to a 12-month rehabilitation program^13^. Current rehabilitation programs based on inpatient supervision have several limitations. One of the most important is the lack of adherence in the medium and long term. At the end of phase II, few patients adopt the advice given for the rest of their lives and continue to do physical activity at the required intensity (phase III). There is a direct relationship between the degree of physical training maintained and cardiovascular morbidity and mortality^14,15^ and therefore some of the benefits achieved are reversed over time. To overcome these limitations, modifications and new strategies to existing programs are probably required. Outpatient rehabilitation programs are being evaluated in recent years as alternative strategies with good results^16^. The development of telematic applications and Internet-based platforms constitute the fundamental tools for carrying out these home-based rehabilitation programs^17^. There are some experiences in which their feasibility has been demonstrated, increasing adherence to physical activity^18^. Their use in conditions of distance from the hospital and their equal or lower cost in some cases are other possible advantages^19^ . The present study is aimed at validating a new Integrated Telerehabilitation System as support for post-infarction rehabilitation, optimising it and testing its usefulness in terms of improving adherence to physical exercise and cardiovascular risk parameters. It should also be analysed whether there are limitations to the use of these technologies by older people with no previous experience in the use of new communication technologies. The economic analysis will make it possible to estimate whether there are added advantages such as cost containment. The importance of these innovations has led the European Union to allocate funds within the Seventh Framework Program to promote new technological developments. The platform and application used in this trial, with the appropriate modifications, are already being used in the follow-up of heart transplant patients ^20^. In a context of rising health system costs, it is important to raise patient awareness of the responsibility of maintaining health by adopting healthier lifestyle habits. Moreover, these innovations in rehabilitation programs can encourage motivation and act synergistically, together with other pharmacological measures, to achieve the prevention objectives that require so much work and effort on the part of all the actors involved.

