## Methods

After explaining the fundamentals of the study to the patients and accepting their participation, they will sign the informed consent form. The first procedure will be to perform a symptom-limited treadmill exercise test with oxygen consumption, seven to ten days after hospital discharge, using the Bruce protocol. If the test results allow inclusion in the study, demographic data, clinical history, physical examination and analytical data will be completed in the data collection notebook. The baseline surveys will be completed, the procedures to be followed will be explained, as well as the schedule of the various activities included in each of the groups. Patients shall receive medication as deemed appropriate by the physician at the time of discharge from hospital, with the initial goal of achieving LDL of 70 mg/dl or less, blood pressure of 140/90 mmHg or less and, where appropriate, glycosylated haemoglobin of less than 7%.

The follow-up period will be 10 months in both groups. The differences in follow-up are detailed below.

At the end of the 10-month follow-up period, all subjects included in the study will undergo a stress test, final analysis and completion of the various outcome evaluation surveys.

Control Group A.

Patients in Control Group A will come to the hospital twice a week during the 8 weeks of the conventional rehabilitation program. Eight sessions will be devoted to physical exercise and another eight sessions to education in various aspects. At the end of the hospital phase, outpatient follow-up by primary and specialised care will be carried out. Subjects will visit the hospital a total of 16 times during 8 weeks to perform the exercises included in the hospital protocol, supervised by a physiotherapist and a nurse from the Cardiology Service.

The protocol includes:

Preparation to start the activity (Warm-up).

15 minutes of low impact cardiovascular exercise plus stretching and flexibility.

Stretching:

8-10 seconds interspersed with activities that maintain heart rate such as walking in place.

Musculature involved: triceps sural, hamstrings, quadriceps, deltoids, paravertebral and pectoralis.

The circuit:

The circuit is designed to cater for all patients with varying functional abilities. It provides the opportunity to increase cardiovascular work time. It is organised as explained in the following diagram:

| **LEVEL** | Group session content |
| --- | --- |
| 1 | 1 CV station followed by 1 min. Of AR |

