***CV Station 3***

WALK

DISTANCE

- Hypertension and cholesterol

- Coronary heart disease

- Cardiovascular drugs

- Heart disease and sex

- Diabetes

- Physical exercise

- Diet

- Tabaco

Intervention Group B.

The patients in Intervention Group B, included in the telerehabilitation program, will attend the hospital twice a week for 2 consecutive weeks, carrying out three sessions of physical exercise and four sessions of education on the same subjects as control group A. Subsequently, they will follow the guidelines programed in the ITS by carrying out their guided physical activities and adherence to the guidelines for management of their risk factors until the end of the study period. All the data generated are recorded in the professional application.

The program consists of two phases: an outpatient phase, in which the patient will attend the hospital 4 times during two weeks; and a second long-term phase of 10 months, where the patient will carry out the entire rehabilitation and prevention program with total independence.

Hospital phase: Starting on the first day, each individual in the patient team is provided with the ITS system described in the materials section. The patient is instructed to perform the programed physical activity and how to use the instrumentation, consisting of the application on the smartphone and the web connection to access the educational content and control of recommended hygienic and dietary measures, as well as monitoring of the pharmacological treatment. Ambulatory physical activity consists of walking at a sustained pace, until the effective heart rate equal to 75% of the maximum heart rate, obtained in the baseline stress test, is reached. The intensity of the exercise will be individually adapted according to the result of this same test. The hospital stay will be about two and a half hours, according to the following schedule:

1st session (Monday)

- Data collection: 60m

- Lecture: Explanation of the program and how the system works: 30m

- First exercise session: 60m

2nd session (Thursday)

- Clarification of doubts about how the system works: 30m

- Talk: Coronary heart disease and cardiovascular risk factors: 40m

- Second exercise session: 60m

3rd session (alternate weeks, Mondays) (12 patients)

- Talk: Anxiety and depression. Strategies to resolve conflicts: 45m.

- Talk: Sexuality and smoking: 45m

- Sketches humour: 30m

4th session (Thursdays)

- Talk: Hypertension and diabetes: 30m

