## Economic evaluation: cost-effectiveness analysis

The study includes a cost-effectiveness analysis to assess the costs and impact on health-related quality of life of the telerehabilitation intervention compared to in-hospital rehabilitation and the control group. The cost analysis will be carried out from the funder's perspective, including direct health care costs (pathology-related emergency visits, hospitalisations for the same cause, diagnostic and therapeutic tests such as revascularisations...) during follow-up. It will also include the costs derived from the intervention, which in the case of conventional rehabilitation, the programd schedule includes 16 rehabilitation visits, 8 rehabilitation sessions (with a physiotherapist, a nurse and a nursing assistant per session) and 8 educational talks. In the telerehabilitation group, the schedule includes 4 rehabilitation visits, 3 sessions (with a physiotherapist and a nurse) and 4 educational sessions. Unscheduled visits and sessions during the follow-up will also be included. The unit costs will be obtained from the Generalitat Valenciana catalogue.

Additionally, an analysis will be performed from a social perspective, including also indirect health care costs due to lost productivity of the patient (number of sick leaves and time to return to work after the event). Indirect costs will be reported by the patient in the follow-up data collection logbook. Effectiveness will be assessed by the physical activity performed by the patient, reported by the patient at the end of the follow-up, measured in METs-minutes/week.

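### The social-perspective cost adds only lost productivity and leaves out patient travel, although the design schedules 16 hospital visits in one arm and 4 in the other

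*Protocol*

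**What the plan says.** Section 9.4 sets out two perspectives. For the first, "The cost analysis will be carried out from the funder's perspective, including direct health care costs" are counted, together with the cost of delivering each programme and any unscheduled visits or sessions. The second, the social perspective, is an additional analysis described as "including also indirect health care costs due to lost productivity of the patient (number of sick leaves and time to return to work". The section says that indirect costs are to be reported by the patient in the follow-up logbook.

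The same section fixes the visit schedule. For conventional rehabilitation, "the programd schedule includes 16 rehabilitation visits"; for telerehabilitation, "the schedule includes 4 rehabilitation visits". Section 6.4 agrees. For control it says "Patients in Control Group A will come to the hospital twice a week during the 8 weeks of the conventional rehabilitation program" and "Subjects will visit the hospital a total of 16 times during 8 weeks". For the intervention group it says "the patient will attend the hospital 4 times during two weeks".

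Section 6.2 recruits both groups from both hospitals, but delivers the control programme at La Fe and the telerehabilitation programme at Arnau de Vilanova. Section 3, on outpatient and home-based programmes in general, remarks: "Their use in conditions of distance from the hospital and their equal or lower cost in some cases are other possible advantages".

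**The concern.** A social perspective is meant to reach beyond the payer. Here it adds one item, lost productivity, and leaves out a patient-borne cost whose volume differs between the arms by design. Each hospital visit is a return trip for the patient, and the control patient has four times as many.

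The productivity item does not stand in for travel. It is measured by sick leaves and time to return to work, so a trip made while the patient is already on leave adds nothing to it. Many trips are likely to fall in that period, because the entry exercise test takes place seven to ten days after discharge. Trips by patients who do not work add nothing either. Patients up to 72 years are eligible, and the logbook itself asks whether the patient was working before the event.

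At stake is how well the social-perspective result describes what each programme costs, in a comparison where fewer hospital visits is one of the main differences between the two programmes.

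**Working it through.** **Visits, reproducing the protocol's own figures**

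- Control (6.4): 2 per week × 8 weeks = 16. The split into 8 exercise and 8 education sessions also gives 8 + 8 = 16. Section 9.4 states 16.
- Telerehabilitation (6.4): 2 per week × 2 weeks = 4. Section 9.4 states 4.
- Assessments at months 4 and 10 are common to both arms and cancel.

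**Trips left out**

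- Per patient: 16 − 4 = 12 more return trips in the conventional arm; ratio 16 / 4 = 4.
- With 30 per arm (9.1): 480 v 120 trips, a difference of 12 × 30 = 360.
- With the 27 per arm used for the power statement: 432 v 108, a difference of 12 × 27 = 324.

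**Is travel captured elsewhere?**

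- Funder perspective (9.4): health care and programme delivery costs. The provider's cost of the 16 and 4 visits is already here; the patient's cost of reaching them is not.
- Social perspective (9.4): sick leaves and return to work are the only additions named.
- Annex 1: the socio-occupational fields are working status before the event at visit 1, then working status and days to return to work at months 4 and 10. There is no field for distance, transport or out-of-pocket cost, and none for attendance at sessions.

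**Money, for illustration only**

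The protocol gives no travel cost, so these unit values are assumptions.

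- Transport at EUR 2 to 40 per return trip: 12 × 2 = EUR 24 to 12 × 40 = EUR 480 per patient, all of it added to the conventional arm.
- Travel time, if valued, at 0.5 to 2 hours per trip and EUR 5 to 15 per hour: 12 × 0.5 × 5 = EUR 30 to 12 × 2 × 15 = EUR 360 per patient.

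**Other patient-borne items not counted**

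Section 6.4 asks telerehabilitation patients to exercise 4 times a week from week 3 to week 40. That is 38 weeks × 4 = 152 sessions, against 8 supervised exercise sessions in the conventional programme. Exercise that control patients do on their own is not quantified. Patient time spent exercising enters neither perspective.

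**The case against.** The strongest reply is that this is a choice and not an error. Section 9.4 says which costs it adds and contradicts nothing else in the protocol. The stated economic objective is only cost per patient per month. The social perspective is a supplement, its wording need not be exhaustive, and an analysis plan that is not available here could add travel from scheduled visits and an assumed distance. Much of this stands, and it keeps the point minor. It does not remove it, because the protocol fixes both the content of the social perspective and its data source. A later plan could impute travel, but could not recover patient-level distance or transport that the logbook never asked for.

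Four stronger readings are tempting, and the documents do not support them.

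- *The social cost as a whole is biased against telerehabilitation.* Omitting travel, taken alone, lowers the conventional arm's cost. Exercise time is uncounted too, and if patient time is to be valued it may weigh the other way. The net direction is unknown.
- *Patient cost differs four-fold.* The number of scheduled trips does; the cost per trip is not given.
- *Only control patients have to attend the other hospital.* Section 6.2 places La Fe recruits in the telerehabilitation group at Arnau de Vilanova as well. The asymmetry is 16 visits against 4, not who crosses over.
- *The plan fails to test an advantage that it claims.* Distance appears in section 3 as background on such programmes, listed beside cost as a possible advantage. No objective in sections 1.7, 1.8 or 4 sets out to test it.

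**Conclusion.** The point holds in a limited form. As written, the social perspective is the funder's costs plus productivity losses. It leaves out patient travel, which differs between the arms by 12 scheduled return trips per patient (360 with 30 per arm). The conventional arm's patient-borne cost is understated as a result.

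The trip count rests only on the protocol's own schedule, assumes full attendance, and sets aside unscheduled visits. The size in euros rests wholly on assumed unit values: EUR 24 to 480 per patient for transport over the range shown. The protocol gives no total or incremental cost against which to judge whether that matters. The finding is a cheap improvement to a secondary economic analysis and has no bearing on the primary comparison.

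**What to change.** In section 9.4, add patient transport cost to the social perspective: scheduled visits × return-trip cost from home to the hospital that delivers the programme. Attended visits would be better, but Annex 1 has no attendance field, so one would have to be added. Record distance and usual means of transport once at baseline in Annex 1. Report the social-perspective result with and without the travel line. Value travel time only as a sensitivity range, since counting one kind of patient time and not another would itself tilt the comparison.

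If the sponsor prefers not to do this, rename the analysis *funder perspective plus productivity losses*, so that the label matches the content.

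The cost is one baseline item, one line in the cost model, and reliance on assumed unit costs that must be stated and varied.

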# Quality Control

The investigators will keep the study documents with clinical follow-up value in their corresponding clinical records as they are not extraordinary procedures. All information collected in the CRFs will be cross-checked with the notes made in the clinical record. The investigator undertakes to complete the CRFs diligently and clearly. The investigator will keep a copy of the informed consent form. informed consent. The study data will be kept for 5 years according to current legislation so that it can be hypothetically reviewed at a later date.

# Monitoring

Monitoring will be carried out through telephone calls to the participating investigators as well as an on-site visit to each participating centre, with the aim of supervising the development of the study and the correct compliance with the SOPs.

The main tasks that are carried out in the monitoring process are

- Summary of the study (inclusion and exclusion criteria, objectives, main objectives of the study, special characteristics of the project).

- Advice on doubts related to the protocol.

- Reminder of Good Clinical Practice procedures.

- Review the correct obtaining of Informed Consent.

- Advice on how to fill in the DCL.

- Monitoring the inclusion of patients

- Verify that the data appearing in the clinical history and in the DCL are the same, as well as checking the appropriate annotations in the patient's clinical history.

The monitor will request the investigator's assistance to diligently carry out his or her tasks.

# Withdrawal of patients from study

The withdrawal of a patient from the study may be due to the Investigator's final decision or the patient's decision to leave the rehabilitation program.

## Criteria for definitive withdrawal from study

A patient may withdraw her consent, if she so chooses, at any time and for any reason, or it may be withdrawn by decision of the Investigator. As far as possible, care should be taken to document the reason for withdrawal and record it in the DCL as:

- At the patient's own request.

- Physician's decision.

## Procedures and Consequences of a patient’s withdrawal from the study

Patients may leave the study if they choose to do so, at any time and for any reason.

If the patient leaves the study for any reason, the patient should be evaluated using the procedure normally provided for the end-of-study visit.

For patients who do not return to the site, the Investigator should make every effort to recontact them (e.g., by contacting their family members or private physician, reviewing available records or the health database) and determine their health status, including at least their vital status. Attempts to contact them should be recorded in the patient's records (e.g. times and dates of telephone contact attempts or proof of sending registered letters).

If LDL cholesterol levels are above 100 mg/dl at 4 months, the patient will be excluded from the study for protocol reasons. If the patient is in the conventional rehabilitation group, medical treatment will be increased and he/she will be followed until the end of the study, although his/her data will not be analysed in the calculation of the results of the study. If you are in the telerehabilitation group, your medication will be increased and you will continue in the program until the end, although, as in the previous case, your data will not be considered for the statistical analysis.

The statistical analysis plan will specify how these patients will be considered.

Patients who have dropped out of the study cannot be readmitted to the study. Their inclusion number should not be used.

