## Definition of the study population: selection criteria

1. Inclusion Criteria

- Patients after uncomplicated acute coronary syndrome of both sexes.
- Completion of a maximal or symptom-limited exercise test without angina or electrical ischaemia.
- Age equal to or less than 72 years.

1. Exclusion Criteria

- Refusal of informed consent
- At the investigator's judgement, primarily due to advanced biological age.
- Severe renal insufficiency (GFR < 30ml/min/1.73 m2).
- EF less than 50%.
- Hepatic insufficiency (GOT >2 times normal value).
- Uncontrolled blood pressure (>140/90 mmHg).
- Uncontrolled heart failure.
- Dissecting aortic aneurysm.
- ventricular tachycardia or other dangerous ventricular arrhythmias that are not controlled (multifocal ventricular activity).
- Aortic or mitral valve disease.
- Recent systemic or pulmonary embolism.
- Active or recent thrombophlebitis.
- Acute infectious diseases.
- Uncontrolled supraventricular arrhythmias or tachycardias.
- Repeated or frequent ventricular ectopic activity.
- Moderate pulmonary hypertension.
- Ventricular aneurysm.
- Uncontrolled diabetes, thyrotoxicosis, myxoedema,
- Hepatic or renal failure and other metabolic insufficiencies.
- Conduction disorders such as: Complete AV block. Left bundle branch block. Wolf-Parkinson-White syndrome.
- Fixed rate pacing.
- Severe anaemia.
- Psychoneurotic disorders.
- Neuromuscular, musculoskeletal and arthritic disorders that may limit activity.

1. Withdrawal Criteria

- Withdrawal of consent to continue the study.
- At the investigator's discretion if appropriate for the patient.
- Need to modify lipid-lowering treatment.
- Unwillingness to continue the study or loss due to dropout.
- Clinical events.
- Other reasons at the discretion of the investigator.

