## Methodology of statistical analysis

The characteristics of the patients in the two study groups will be described (applying the appropriate estimators according to the type of variables, such as means and confidence intervals, medians and interquartile ranges or proportions) and possible differences between the groups will be assessed using appropriate statistical tests of differences of means, distributions of ranks or proportions. The comparison of the primary variable and the secondary variables of the study in both groups at baseline, at four months and 10 months after the start of rehabilitation will be carried out using Pearson χ2 test for qualitative variables (Fisher exact test for dichotomous variable) or Student t-test for independent samples for quantitative variables (Mann-Whitney U test when parametric assumptions couldn’t be assumed). The treatment effects within groups (at four months or ten months) will be assessed using McNemar-Bowker test of symmetry for qualitative variables (McNemar test for dichotomous variable) or Student t-test for paired samples for quantitative variables (Wilcoxon signed-rank test when parametric assumptions couldn’t be assumed). The relationship between quantitative variables will be assessed by Pearson’s correlation coefficient (Spearman’s rank correlation coefficient when parametric assumptions couldn’t be assumed). Multiple linear regression models will be used to assess the significance and magnitude of the intervention effect controlling for possible differences in patient characteristics between groups. In general, backward-forward models will be used, initially constructing the complete models and excluding non-significant variables one at a time (p for variable removal: 0.10) but trying to include the previously removed variables after each exclusion (p for incorporation: 0.05. The analysis will be performed on an intention-to-treat basis. For the economic evaluation, the unit cost will be obtained by quantifying the consumption of resources and applying the official cost rates of the Valencian Health Agency or, if these are not available, they will be estimated by assessing the time and cost of the resources involved. Two-sided exact p-values will be calculated whenever possible and p-values ≤ 0.05 were considered statistically significant. Data will be analysed using IBM SPSS Statistics 22 and R 4.0.2 for Microsoft Windows.

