## Interference with individual doctor's prescribing habits

The use of drugs is not evaluated in this study. The drugs prescribed at discharge from hospital can be modified by the various physicians doing the clinical follow-up with the aim of achieving optimal care for each pathology or improvement of cardiovascular risk factors. At discharge, the appropriate statin will be prescribed at the appropriate dose to hypothetically achieve a lowering of LDL cholesterol below 70 mg/dl according to the percentage of LDL lowering recognised for each statin and dose. During the study there will be no dose modification except for LDL levels above 100 mg/dl at 4 months, in which case the patient will be withdrawn from the study, as this variable is one of the efficacy parameters evaluated within the new telemonitoring strategy. Obviously, the patient will patient will obviously remain in the telerehabilitation program, although his or her final data will not be evaluable.

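### The protocol drops the data of patients with LDL above 100 mg/dl at 4 months, which contradicts its intention-to-treat statement and selects the analysed set on an efficacy variable measured after randomisation

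*Protocol*

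**What the plan says.** Section 12.2 (Procedures and Consequences of a patient's withdrawal from the study) sets the rule: "If LDL cholesterol levels are above 100 mg/dl at 4 months, the patient will be excluded from the study for protocol reasons". For a conventional-arm patient, treatment is increased and follow-up continues to the end, but "his/her data will not be analysed in the calculation of the results of the study". For a telerehabilitation patient, medication is increased and the programme continues, but "your data will not be considered for the statistical analysis". The next sentence reads: "The statistical analysis plan will specify how these patients will be considered".

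Section 13.5 (Interference with individual doctor's prescribing habits) repeats the rule and gives the reason: "the patient will be withdrawn from the study, as this variable is one of the efficacy parameters evaluated within the new telemonitoring strategy". The patient stays in the programme, "although his or her final data will not be evaluable". That section does not refer to the SAP.

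Section 6.3 lists among its withdrawal criteria "Need to modify lipid-lowering treatment".

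Section 9.3 (Methodology of statistical analysis) says "The analysis will be performed on an intention-to-treat basis", as does Data Analysis in the summary. Lipid profile is a secondary objective, and LDL is collected at baseline, 4 and 10 months. The primary variable, METs-minutes/week from the IPAQ, is judged at 10 months.

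**The concern.** An intention-to-treat comparison keeps every randomised patient in the assigned arm. Here patients are removed on a value obtained 4 months after allocation. The telerehabilitation programme works on diet, exercise and risk factors and sends medication reminders, so it can change who crosses 100 mg/dl. The protocol itself calls LDL an efficacy parameter. Patients who do badly on an efficacy outcome are therefore removed from the efficacy analysis, and no outcome, including the primary, is exempted.

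Three things are at stake. The LDL comparison loses its upper tail. The primary comparison loses the protection of randomisation wherever the arms exclude different proportions or kinds of patient. And the loss comes on top of the 12% allowance in section 9.1, which covers loss to follow-up only.

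**Working it through.** **Side by side.** Section 12.2 (both arms) and section 13.5 say the data are not analysed or not evaluable. Section 9.3 and the summary say intention-to-treat. Section 12.2 also says the SAP will decide. The contradiction needs no arithmetic; the figures below show only its possible size.

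**The plan's power figure.** Section 9.1 gives 27 per arm, two-sided alpha 0.05, means of 5000 and 4000, and power 95%, with no SD. Solving the two-sample t-test for the SD gives 1000. With that SD the standard error is 1000 × √(1/27 + 1/27) = 272, and the power is 95.0%.

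**4-month LDL: direct truncation.** Assumed, because the documents give none: normal distributions with SD 25 and a true difference of 10 mg/dl. With k = (100 − mean)/25, the excluded share is 1 − Φ(k), and the mean of those kept is mean − 25 × φ(k)/Φ(k).

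- Mean 90: k = 0.4, 34% excluded, kept mean 90 − 25 × 0.562 = 76.0.
- Mean 80: k = 0.8, 21% excluded, kept mean 80 − 25 × 0.368 = 70.8.
- Mean 70: k = 1.2, 12% excluded, kept mean 70 − 25 × 0.219 = 64.5.

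Control 80 against telerehabilitation 70: 70.8 − 64.5 = 6.3. Control 90 against 80: 76.0 − 70.8 = 5.1 from unrounded means.

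**10-month LDL: indirect.** Assume the same means and SD, a 4-to-10-month correlation r and no medication change. The kept mean is then mean − r × 25 × φ(k)/Φ(k).

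- 80 against 70: 8.9 at r = 0.3 and 7.4 at r = 0.7.
- 90 against 80: 8.5 at r = 0.3 and 6.6 at r = 0.7.

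**Primary variable: shift under no true effect.** Assume METs SD 1000 and correlation ρ with 4-month LDL. The shift in each arm is −ρ × 1000 × φ(k)/Φ(k).

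- Equal exclusion and equal ρ in both arms: the shifts cancel, so the bias is 0 and type I error is 5.0%.
- 30% of controls and 10% of telerehabilitation patients excluded: φ(k)/Φ(k) is 0.497 and 0.195. At ρ = −0.5 the shifts are +248 and +97, a spurious difference of about 151 METs-minutes/week against telerehabilitation, with type I error about 7.7%. At ρ = −0.2 and −0.3 the differences are about 60 and 91, with type I error about 5.4% and 6.0%.

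**Power.** Loss to follow-up leaves 30 × 0.88 = 26.4, taken as 26 per arm. Fractional results below are rounded to whole patients.

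- 21% and 12% excluded: 26 × 0.788 = 20.5 and 26 × 0.885 = 23.0, taken as 21 and 23. Power is 90%.
- 34% and 21% excluded: 26 × 0.655 = 17.0 and 26 × 0.788 = 20.5, taken as 17 and 21. Power is 85%.

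**The case against.** The best defence is that section 12.2 hands these patients to a SAP that is not shown, and the SAP may keep them. That stands to this extent: the final analysis set is not known. It does not rescue the protocol, because the deferral follows two sentences that already fix non-analysis and section 13.5 repeats the rule without any deferral.

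The size may also be small. Section 13.5 says statins are chosen with the aim of bringing LDL below 70 mg/dl. At a mean of 60 and SD 25 only about 5% would exceed 100. This is fair, and it is why every figure here is an illustration.

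Several stronger readings are tempting but unsupported:

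- A reader might infer that everyone withdrawn under section 6.3, including for clinical events, leaves the analysis. That section lists reasons for withdrawal and does not say the data are discarded. Section 12.2 asks for the end-of-study evaluation when a patient leaves.
- A reader might take the 51% dyslipidaemia in the rationale as a guide to the exclusion rate. It is a survey figure with no LDL cut-off, outside this protocol's statin policy.
- A reader might say that only lipid responders are kept. LDL at or below 100 is a level, not a response.
- A reader might apply the 6.3 and 5.1 mg/dl figures to all lipid results. They apply to 4-month LDL only; 10-month LDL and the other lipids are affected only through correlation. Section 13.5 speaks only of final data, so on that wording the 4-month values might even be kept, though section 12.2 is broader.
- A reader might expect a false claim of superiority on the primary. In the scenario worked above the shift goes against telerehabilitation, and with equal exclusion and equal correlation there is none.

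**Conclusion.** Wrong as written. The exclusion in sections 12.2 and 13.5 cannot stand beside the intention-to-treat statement, and it selects the analysed set on a post-randomisation efficacy variable. That conclusion rests on the text alone.

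The size rests on assumptions. With means of 80 and 70 and SD 25, a 10 mg/dl difference becomes 6.3 at 4 months and about 7.4 to 8.9 at 10 months. For the primary variable, neither the size nor the direction of bias can be determined from the protocol. The loss of power is secondary: from 95% to about 90% or 85% in the two scenarios, given the back-solved SD of 1000.

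**What to change.** Delete the wording in sections 12.2 and 13.5 that makes these data non-analysable or non-evaluable. State that all randomised patients are analysed in their assigned arm with all data collected, whatever the 4-month LDL. Record a change of lipid-lowering treatment as an intercurrent event, with a sensitivity analysis for the lipid endpoints. State that withdrawal under section 6.3 does not by itself remove data already collected from the analysis.

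Reconcile sections 6.3, 12.2 and 13.5. This includes section 13.5's statements that physicians may modify drugs and that doses are not modified except above the LDL threshold. The clinical withdrawal criteria and the management of LDL are not judged here and need not change.

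For the patients above the LDL threshold the cost is wording only, since section 12.2 already follows them to the end. For patients withdrawn on other grounds, the change keeps what was collected; it does not supply 10-month values that were never obtained. The small downside is that lipid results will include patients whose medication was changed, which the sensitivity analysis addresses.
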